### Data Management and Data Analyses

#### Data Management

Clinical and paraclinical data as well as the results of the genetic analyses carried out will be entered directly into the dedicated e-CRF by the investigators, helped by CRTs and by biologists and bioinformatics specialists in charge of the GS analyses. The patient diary specific to microcosting and patient follow-up are in paper or electronic format (forms independent of the e-CRF). Each patient is identified by a unique code including: the number of the recruiting center, the inclusion rank, the initials of the patient (first letter of surname and first letter of first name) and a code corresponding to his/her sex. The use of the CleanWEB software makes it possible to carry out checks for missing and incoherent data, and to generate queries immediately after data entry. Requests for corrections may also be generated by the CIC-EC1432 and sent to the recruiting center and/or the reference laboratory. The corrections will be made directly in the e-CRF by the investigators and/or the biologists, assisted by the CRTs. Histories of changes are systematically recorded. A data management plan, specific to the study, integrating centralized monitoring (enabling, for example, comparative monitoring of the distribution of subpopulations between centers and indicators of the quality of sample processing) was prepared before initiating the study in the participating centers.

#### Statistical Analyses

The percentage of ID causal diagnosis identified will be compared between strategies (GST vs reference strategy) using a McNemar test in the overall first-investigation population, then in the seven subgroups of interest. To account for multiple testing, the unilateral alpha risk is set at 0.00278, and also for the secondary comparisons of the diagnostic yield of GST vs. GSS, which will be performed in the dedicated randomized subgroup.

McNemar tests (unilateral alpha risk set at 0.025) will also be used to compare the percentage of causal diagnoses identified by GS and reference strategies in the sub-groups of the individuals coming for a first genetic referral without major non-cerebral abnormality or without epilepsy. This test will also be used in the overall population (first-investigation patients and previously investigated patients) to compare the percentage of causal diagnoses identified by GS strategies in patients with negative CMA. The percentage of causal structural changes identified by GST vs the reference minimal strategy will also be compared using McNemar tests in the first-investigation population (firstly considered all together, and then stratified by subgroups). The number and type of consistent and divergent variants identified with CMA and GS strategies will also be described. The frequency and characteristics of the situations where the causal diagnosis is identified by the reference strategy but not by the GS analyses will be described, as well as the frequency and characteristics of situations where the causal diagnostic is made by GSS and not by GST.

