The strategy based on GST is expected to yield a diagnosis in at least 60% of patients with ID versus 30% with the reference minimal strategy in the population of patients attending for a first genetic investigation (never-explored patients). However, the strategies will be compared in 7 subgroups: 1) 3 defined by age: children <2 years old/2–5 years/>5 years; 2) 4 subgroups of patients defined according the severity of ID, and/or 3) with associated manifestations:1) mild ID associated with another sign, 2) moderate to severe ID, 3) ID with major non-cerebral abnormality, and 4) ID associated with epilepsy The smallest sub-group (subjects with mild ID associated with another significant sign) should represent around 15% of the total population, and the difference between the GST and the reference strategy in this particular subgroup can be assumed to be less than 15%. In addition, it is assumed that fewer than 1% of diagnoses identified with the referral minimal strategy will not be identified by the GST. Finally, we will also compare GST and GSS in a subgroup of randomized patients referred for the first time. For this specific comparison, a difference of 7% is expected, and <0.1% of diagnoses identified by GSS and not by GST. Considering these 9 planned comparisons (8 comparisons between GST and the reference strategy and 1 between GST and GS), the one-sided alpha risk is fixed at 0.00278. Based on these hypotheses, and a power of 80%, among patients seen for a first genetic investigation (50% of the population to be recruited), 41 patients are required for the main comparison, and 91 patients with mild ID + other syndrome are necessary. To recruit this number of patients, we estimate that it will be necessary to screen 607 patients attending for a first referral. A subgroup of 196 patients will be randomized to undergo GSS in addition to GST plus the reference minimal strategy. The sample size for this subgroup will be sufficient to compare GST and GSS in terms of diagnostic yield, as well as in terms of efficiency (a sample size over 150 is usually deemed sufficient). As we intend to include 50% of patients attending for a first genetics evaluation (never-explored patients), and 50% of patients who have already been investigated (previously-explored patients), a total of 1,214 patients are necessary. Considering that approximately 5% of samples will not be analyzable, it will therefore be necessary to include 1,275 index cases plus both their parents, for a total of 3,825 participants.

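### The fixed one-sided 0.00278 for all nine comparisons is valid, but Holm's step-down over the same nine tests gives the same error control and more power where it is tightest

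*Protocol article*

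**What the plan says.** The sample-size paragraph under Population defines the family: "Considering these 9 planned comparisons (8 comparisons between GST and the reference strategy and 1 between GST and GS"). It then sets the level: "the one-sided alpha risk is fixed at 0.00278". The trial is sized at that level: 41 patients for the main comparison and 91 with mild ID plus another sign. The 91 lead to 607 first-referral patients, 1,214 in all, and 1,275 after allowing for 5% unanalysable samples. A further 196 are randomised to have GSS as well.

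The Statistical Analyses section repeats the rule: "To account for multiple testing, the unilateral alpha risk is set at 0.00278". GST and the reference strategy are compared "using a McNemar test in the overall first-investigation population, then in the seven subgroups of interest", and the same level extends to the trio-versus-solo comparison. No sequential or step-down procedure is stated.

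The next paragraph adds tests at a different level: "McNemar tests (unilateral alpha risk set at 0.025) will also be used". These include first-referral patients without a major non-cerebral abnormality and those without epilepsy. The corresponding subgroups with these features belong to the nine.

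**The concern.** A fixed Bonferroni level does not change as hypotheses are rejected. Holm's procedure tests the smallest p-value at 0.025/9, the next at 0.025/8, and so on to 0.025 for the last. It needs no assumption about the correlation between tests, which suits overlapping subgroups, and it rejects everything that Bonferroni rejects. The fixed level therefore gives up power for no gain in error control.

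The loss falls on the tests with least room: the smallest subgroup and, to a lesser degree, trio versus solo. Both bear on stated aims of the study, namely which strategy suits which clinical presentation and whether solo sequencing is good enough when parents are unavailable.

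There is also an uneven threshold. Patients with epilepsy or a major non-cerebral abnormality are tested at 0.00278. Their complements in the same first-referral population are tested at 0.025, nine times looser and outside the family.

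**Working it through.** **Inputs, all from the sample-size paragraph under Population**
- Nine comparisons, one-sided, with "Based on these hypotheses, and a power of 80"%.
- Main comparison: the trio strategy is "expected to yield a diagnosis in at least 60% of patients with ID versus 30% with the reference minimal strategy", a difference of 0.30. Reference-only diagnoses are below 1%, taken as 0.01.
- Mild ID: difference below 15%, taken as 0.15; reference-only 0.01.
- GST versus GSS: difference 0.07; GSS-only below 0.1%, taken as 0.001.

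**Method.** Exact one-sided McNemar test: a binomial test on the discordant pairs, with power averaged over the binomial number of discordant pairs. With p01 the probability that only the comparator finds the diagnosis, p10 = difference + p01.

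**Step 1: reproduce the plan.**
- Level: 0.025/9 = 0.00278.
- Main (p10 0.31, p01 0.01): n = 41 is the first size to reach 80% (0.809; n = 40 gives 0.789).
- Mild ID (0.16, 0.01): n = 91 is the first size to reach 80% (0.803; n = 90 gives 0.795).
- GST versus GSS (0.071, 0.001): n = 169 reaches 80%, and n = 196 is the first size to reach 90% (0.902).
- 91/0.15 = 607 and 2 × 607 = 1,214. Also 637 × 0.95 × 0.15 = 91, so the 91 is already net of the 5% loss.

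The plan is internally consistent at this level.

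**Step 2: power at the fixed level and at Holm's last two levels.**

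| Test | 0.00278 | 0.0125 | 0.025 |
|---|---|---|---|
| Main, n = 607 | 1.000 | 1.000 | 1.000 |
| Mild ID, n = 91 | 0.803 | 0.939 | 0.965 |
| GST vs GSS, n = 196 | 0.902 | 0.977 | 0.989 |

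**Step 3: power under Holm.** Suppose the other seven tests reject and treat the last two as independent. Then

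P(reject A) = P(pA ≤ 0.0125) + P(0.0125 < pA ≤ 0.025) × P(pB ≤ 0.0125).

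- Mild ID: 0.939 + (0.965 − 0.939) × 0.977 = 0.964.
- GST versus GSS: 0.977 + (0.989 − 0.977) × 0.939 = 0.988; 0.989 with unrounded inputs.
- Both rejected: 0.803 × 0.902 = 0.724 with Bonferroni, 0.954 with Holm.

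A simulation with overlapping subgroups, whose shares other than mild ID had to be assumed, gave 0.97 and 0.99 under Holm.

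**Step 4: error control in that simulation.** Under the global null the familywise error was 0.012 for both rules. With only the two hardest hypotheses null it was 0.003 for Bonferroni and 0.013 for Holm. All are below 0.025.

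**Step 5: smaller mild-ID differences (illustrative, n = 91).**

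| Difference | Fixed 0.00278 | Holm, other seven reject |
|---|---|---|
| 0.15 | 0.80 | 0.96 |
| 0.12 | 0.59 | 0.89 |
| 0.10 | 0.41 | 0.78 |

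**The case against.** The strongest reply is that nothing here is wrong. Bonferroni is valid, the two sections agree on it, and the trial was sized at that level and reaches its target power. That stands: the point concerns efficiency, not a false error rate.

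Three stronger readings are tempting and should not be drawn.
- A reader might infer that the primary comparison is weakened because it shares the level. It needs 41 patients and has about 607.
- A reader might infer that trio versus solo is underpowered. At the planned 7-point difference it has 90% power with 196 patients, and still 87% with 186 (196 less about 5%).
- A reader might infer that the two alpha levels will produce a spurious contrast between patients with and without epilepsy. This is unlikely at the planned effects. Mild ID is described as the smallest subgroup, so the epilepsy subgroup should have at least about 91 patients. With a 30-point difference, the chance that its p-value falls between 0.00278 and 0.025 is about 0.0004; with 20 points it is about 3%. The 0.025 tests appear as further analyses, and the article nowhere plans to infer a contrast from one significant and one non-significant result.

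The Holm gains also depend on the other seven tests rejecting. The article gives no expected effect for six of them, so 0.96 and 0.99 are close to the best case. Finally, Bonferroni yields simple simultaneous confidence bounds, which are useful in a study of diagnostic yield. Holm's are harder to construct and often uninformative for rejected hypotheses.

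**Conclusion.** The point holds as a cheap improvement, not as an error. Holm over the same nine tests keeps the one-sided familywise error at 0.025 under any dependence and is never less powerful. At the plan's own effects the gain is about 16 percentage points in mild ID and about 9 for GST versus GSS, with none for the primary test. This assumes that the other seven tests reject and that discordance is at the stated bounds.

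The case is strongest in mild ID. The 91 patients are what a difference of 15 points requires, yet the article gives 15% as a ceiling. At 0.00278 there is almost no slack, and a smaller true difference takes power below 80%. The 10-point row is an illustration, as the document gives no such figure.

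The 0.025 level for the two complement subgroups is a minor inconsistency. They sit outside the controlled family without being labelled exploratory, so a superiority claim from them would not be covered by the 0.025.

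**What to change.** By dated amendment, before the comparative results are unblinded:

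1. Replace the fixed 0.00278 with Holm's step-down over the nine listed comparisons (0.025/9, 0.025/8, …, 0.025), each by one-sided McNemar test.
2. Report the subgroups without major non-cerebral abnormality and without epilepsy as estimates with 95% confidence intervals and no superiority claim. Adding them to the family would make eleven tests with a first step of 0.025/11, for which the power figures above do not apply.

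Sample size, data collection and patient care do not change. The text is short, but timing matters: the Trial Status section reports 955 patients already included, and sequencing results are due 6 to 9 months after inclusion. The amendment should therefore state that no comparative results had been seen. The lasting cost is the loss of simple simultaneous confidence bounds; unadjusted 95% intervals can still accompany every comparison.

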Specifically, the primary objective of this study is to compare the percentage of causal genetic diagnosis identified by GS performed on a trio (the patient and both parents) (GST), to the use of the current French reference minimal strategy (Fragile X + CMA + 44GPS) in ID patients attending a first genetics consultation. Secondary objectives focus on the diagnostic yield, and include the following:• To compare the percentage of ID causal diagnosis identified by GST, to GS in the proband only (i.e., genome in solo, GSS) in a subgroup of randomized patients attending for a first genetic investigation. This evaluation is useful because in genetic counseling, both parents are not always available.• To describe the estimated additional diagnostic yield that would be obtained at each step in sequential analysis of the GS data: for the minimal 44GPS gene panel, the list of genes known to be associated with disease from OMIM (referred to simply as OMIM), and ES, in patients attending for a first investigation (never-explored patients) and in patients who have already undergone investigations (previously-explored patients).• To compare the percentage of causal diagnosis of ID identified by GST to that obtained with the French reference minimal strategy in various subgroups (defined according to age, severity of ID, presence of major non-cerebral manifestations or epilepsy), for patients with ID attending for a first genetic investigation (never-explored patients).• To compare the percentage of causal structural changes (CNV, balanced structural variants) identified by GST versus CMA.• The DEFIDAG study also aims to compare the reference strategy, GST and GSs, in terms of costs and effectiveness for the causal diagnosis of ID in patients with ID of unknown etiology, attending for a first genetic investigation.• Finally, three impact studies are planned. The first will estimate the costs associated with searching for a molecular diagnosis that could potentially be avoided by performing GS as the first line approach. The second will evaluate the impact on the frequency and type of medical, medico-social and psychological care in the year following the release of GS results, compared to care during the year prior to inclusion, in particular in patients who were already engaged in a diagnostic process prior to being invited to participate in the DEFIDIAG study. The third impact study will be performed in two centers, and will use a qualitative approach, namely interviews with a sample of parents, to explore: 1) the burden experienced by the parents, 2) emotional adjustment of the patient and the parents to the results of genetic tests, and 3) the patient and parents’ perception of the future.

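### Two, and plausibly three, supportive McNemar tests run at an uncorrected one-sided 0.025 after nine comparisons have spent it, and the structural-change tests have no stated alpha

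*Protocol article*

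**What the plan says.** The sample-size text in the Population section sets up one controlled family: "Considering these 9 planned comparisons (8 comparisons between GST and the reference strategy and 1 between GST and GS), the one-sided alpha risk is fixed". The level given is 0.00278. The eight GST-versus-reference comparisons are the overall first-investigation population and seven subgroups. Two of those subgroups are ID with a major non-cerebral abnormality and ID with epilepsy.

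The first paragraph of Statistical Analyses repeats the rule: "To account for multiple testing, the unilateral alpha risk is set at 0.00278". It applies the same level to GST versus GSS.

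The second paragraph adds tests outside this family:

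- **Complementary subgroups.** "McNemar tests (unilateral alpha risk set at 0.025) will also be used to compare the percentage of causal diagnoses identified by GS and reference strategies". This covers first-referral patients without a major non-cerebral abnormality or without epilepsy. The 0.025 is printed here.
- **CMA-negative patients, whole study population.** The sentence says that the same test will be used. No alpha is repeated.
- **Causal structural changes.** McNemar tests "in the first-investigation population (firstly considered all together, and then stratified by subgroups"). No alpha is given, and the subgroups are not counted or named.

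The last item answers a secondary objective listed in the Introduction: "To compare the percentage of causal structural changes (CNV, balanced structural variants) identified by GST versus CMA". The article states no order, correction or exploratory status for any of these additional tests.

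**The concern.** The sponsor recognised multiplicity, corrected one family for it, and then wrote an uncorrected level for further tests of the same kind. That is a rule fixed in the text, not a detail left to a later analysis plan.

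There are two consequences. First, the two halves of one clinical split face different thresholds. GST versus reference needs p ≤ 0.00278 in patients with epilepsy but only p ≤ 0.025 in those without, and the same holds for major non-cerebral abnormality. With p = 0.01 in both halves, one would be called positive and the other not, because of the assigned alpha alone. The abstract says the study aims to identify the best strategy by clinical presentation, so an artefact of this kind falls on a stated aim.

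Second, the level for a named secondary objective is unclear. The Introduction raises GS as a possible replacement for CMA, and a structural-change result would be read in that light. A reader of the eventual report could not tell which threshold had been planned.

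**Working it through.** **1. Reproduce the plan's alpha.** Inputs from Population: nine comparisons, 0.00278 each.

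0.025 / 9 = 0.002778, which rounds to 0.00278. Total: 9 × 0.002778 = 0.025. Nothing is left for other tests.

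**2. Confirm that the sample size rests on that alpha.** Exact conditional McNemar power at one-sided 0.00278, with the differences of 30 and 15 points and a reverse discordance of 1% (the plan's upper bound):

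- n = 41, discordant proportions 0.31 / 0.01: power 0.809
- n = 91, discordant proportions 0.16 / 0.01: power 0.803

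Both match the stated 80%, so 0.00278 one-sided is the operative level of the controlled family.

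**3. Count the additional tests.**

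- 0.025 printed: 2 (without major abnormality, without epilepsy)
- 0.025 plausibly carried over: 1 (CMA-negative)
- No alpha stated: 1 overall structural test, plus 7 if the seven subgroups of the Population section are meant (assumption)

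2 + 1 + 1 + 7 = 11 on the widest reading.

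**4. Ratio of thresholds within one split.** 0.025 / 0.00278 ≈ 9.

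**5. Chance of at least one false positive.** All nulls true, tests independent, k additional tests at 0.025: 1 − 0.975^k. With the nine included: 1 − 0.975^k × (1 − 0.002778)^9.

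| Reading | k | Sum of alphas, additional tests | Additional tests only | With the nine |
|---|---|---|---|---|
| 0.025 as printed | 2 | 0.050 | 0.049 | 0.073 |
| plus CMA-negative | 3 | 0.075 | 0.073 | 0.096 |
| plus eight structural tests | 11 | 0.275 | 0.243 | 0.262 |

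The tests share patients, so these are illustrations and the sums are upper bounds. Simulation of equicorrelated normal tests at 0.025 gives:

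- k = 3: 0.063 at correlation 0.5, 0.050 at 0.8
- k = 11: 0.152 at correlation 0.5, 0.090 at 0.8

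**6. Structural tests with overlapping subgroups.** Patient-level simulation of the overall and seven subgroup tests at 0.025 each, N = 607. The subgroup shares are assumed: ages 20/40/40%, mild 15%, moderate-severe 60%, major abnormality 40%, epilepsy 25%. Results for assumed structural discordance of 2 / 4 / 8%:

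- asymptotic McNemar: 0.103 / 0.133 / 0.136
- mid-p: 0.058 / 0.103 / 0.124
- exact: 0.022 / 0.055 / 0.079

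The result depends strongly on the version of the test. The exact test at 2% discordance shows no inflation.

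**7. Would the nine-fold gap change a conclusion?** With the assumed 25% epilepsy share, 0.25 × 607 ≈ 152 patients. Exact power at 0.00278 with a 15-point gain (0.16 / 0.01) is 0.988, and above 0.999 at 30 points.

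**The case against.** The strongest reply is that little practical harm follows where 0.025 is actually printed. The plan expects 60% versus 30%, with fewer than 1% of reference diagnoses missed by GST, and the 44-gene result is filtered from the same genome data. A true null in the complementary subgroups is remote. By step 7, both halves of the epilepsy split would almost always pass 0.00278, so the unequal thresholds would rarely alter a conclusion. This stands and limits the weight of the point.

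It is also fair that the claims for which the study is sized (overall, seven subgroups, GST versus GSS) stay controlled at 0.025 in total, and that the order or status of secondary tests is often left to the full protocol or analysis plan. The first part stands. The second does not remove the point: an article may omit a hierarchy, but this one prints an uncorrected level beside a corrected one.

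Two stronger readings are tempting and are not supported:

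- A reader might infer about eleven tests, each at a full 0.025, with a false-positive chance of 0.24. The structural-change sentence gives neither an alpha nor a number of subgroups, and 0.24 also needs independence, which patients shared between tests rule out.
- A reader might infer that the structural-change null is especially plausible because CMA already finds most causal CNVs. The article does not say so. Its Introduction expects greater CNV accuracy from GS and the detection of balanced variants.

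**Conclusion.** The point holds in a limited form. Two supportive tests are explicitly set at an uncorrected 0.025 after the controlled family has spent the whole amount. A third plausibly inherits that level, and the structural-change tests have no stated level. The asymmetry between the with and without subgroups follows directly from the text and needs no assumption.

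The false-positive chance for the additional tests is 0.049 to 0.073 under independence with all nulls true, against a nominal 0.025. Larger figures require that 0.025 also governs the structural tests and that the seven subgroups are meant. Even then, shared patients or an exact test reduce them. The primary comparison and the other eight controlled comparisons are not affected. This is a defect in the rule for secondary claims, worth correcting because the correction costs almost nothing.

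**What to change.** In the second paragraph of Statistical Analyses, drop the 0.025 level and state that every McNemar test outside the nine comparisons is exploratory, reported as a paired difference with a 95% CI and no claim of significance.

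If the overall structural-change comparison is meant to carry a claim, state its alpha and test it only after the controlled family has succeeded. Its subgroup versions, the two complementary subgroups and the CMA-negative test stay exploratory.

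Present the results with and without epilepsy, and with and without major non-cerebral abnormality, side by side at the same CI level.

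This leaves 0.00278 and the sample size unchanged and needs no further patients or data. Spreading one Bonferroni correction over all 20 tests would be worse: 0.025 / 20 = 0.00125, at which exact power falls to 0.725 at n = 41 and 0.727 at n = 91. The cost of the recommended wording is that p-values between 0.00278 and 0.025 in these tests can no longer be presented as confirmed findings.
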